## Abstract

**Background:**

Type 2 Diabetes Mellitus (T2DM) has become an endemic disease. A number of interrelated factors increase the risk of the onset of T2DM, however much of the pathogenesis of the disease is associated with lifestyle. A number of studies have indicated that adopting positive lifestyle changes can successfully prevent or delay the onset of T2DM in a number of different population groups. The CHIP intervention is a lifestyle program that has been shown in over more than 30 published papers have indicated that the CHIP intervention leads to dramatic improvement in the indicators of T2DM these diseases of lifestyle.

**Methods:**

A randomized control trial will be conducted involving 150 individuals with an established diagnosis of T2DM. All participants will continue to receive usual ongoing diabetes care, however, the intervention group (75 individuals) will in addition participate in a 12-week CHIP lifestyle intervention programme followed by a further 9 months of monthly follow-up appointments. Approval for funding was obtained on 30 June 2017.

**Discussion:**

The outcomes of this study have the potential to inform decisions about patient treatment and potentially provide incentive for the provision of funded lifestyle-based preventive and restorative programs for patients diagnosed with T2DM.

**Trial registration:**

This trial is registered as an initial version with the Australia New Zealand Clinical Trials Registry (http://www.anzctr.org.au/), registration number ACTRN12617001233314. Registered on 23/08/2017. No enrollments in the study to date.

## Background

Type 2 Diabetes Mellitus (T2DM) has become an endemic disease [1]. A number of interrelated factors increase the risk of the onset of T2DM, however much of the pathogenesis of the disease is associated with lifestyle, particularly the lifestyle habits associated with obesity [2].

The relationship between the onset of insulin resistance and the presence of obesity has been recognized for decades and is present in all ethnic groups and across the full spectrum of age, gender and body weight [3–5]. Both total and central (intra-abdominal) adiposity are strongly linked to insulin resistance as well as to other metabolic variables including increased plasma glucose, insulin, blood pressure, total cholesterol, low density lipoprotein (LDL) cholesterol and triglyceride concentrations and decreased plasma high-density lipoprotein (HDL) cholesterol concentration [6, 7].

Data from the DECODE study [8] indicated that myocardial infarction (MI), stroke or non-ischaemic cardiovascular disease cause 80% of deaths among patients with T2DM and over 60% of people having T2DM will develop cardiovascular disease. Indeed, T2DM and associated insulin resistance have been recognized as factors that independently increase the risk of cardiovascular morbidity and mortality. They also act synergistically with other major risk factors for cardiovascular disease such as smoking, hypertension and dyslipidaemia to increase cardiovascular disease risk [9].

A number of studies have indicated that adopting positive lifestyle changes can successfully prevent or delay the onset of T2DM in a number of different population groups [10–13]. Lifestyle changes recommended in these studies relate to those associated with reducing obesity such as increasing physical activity levels and consuming a low energy-density diet [13]. The eating pattern recommended in these studies was largely comprised of plant based foods that are low fat and cholesterol but high in fibre, which is in contrast to the traditional Western diet.

The Complete Health Improvement Program (CHIP) is a lifestyle intervention that was primarily designed to reverse coronary artery disease (CAD). Since its inception in 1988, researchers have become increasingly aware that the intervention was also effective in improving clinical outcomes for diseases like hypertension and T2DM. More than 30 published papers have indicated that the CHIP intervention leads to dramatic improvement in the indicators of these diseases of lifestyle. [14–17].

With no known medical cure for T2DM as well as the current and predicted increasing prevalence of the disease, it is important that the benefits of improved lifestyle in the population with diabetes continue to be explored. Increasing healthcare costs associated with chronic diseases and their complications make it necessary to employ programs that are effective and demonstrate a cost benefit.

## Methods/design

### Aims and research questions

There are two aims of this study:To assess the effectiveness of the CHIP intervention in reversing abnormal fasting blood sugar levels in people with T2DM.To determine the cost benefit of the CHIP intervention for persons with a diagnosis of T2DM.

The study will address three main questions;

In a diabetic population within a general practice group on the Central Coast of New South Wales, Australia:When compared to a control group receiving routine diabetic care, what changes occur in fasting blood sugar levels (FBSL), HBA1c, fasting lipogram with triglycerides (FLT), blood pressure (BP), abdominal girth, body mass index (BMI) and medication use among  individuals participating in the CHIP intervention delivered over a period of 12 weeks with additional monthly follow up for another 9 months?Over a 12-month period, what levels of compliance with the intervention are observed in participants?When compared to routine diabetic care, what is the cost benefit (over a 12-month period) of implementing a CHIP intervention delivered over a period of 12 weeks with an additional follow up for another 9 months?

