### Study participants

Patients, who have a diagnosis of T2DM will be recruited from general practice medical centers (where practitioners have agreed to refer) on the Central Coast of NSW, Australia. Recruited patients will be invited to participate in the study. Enrollment of consenting participants will continue until the required sample size is met. The source population will be monitored at each participating General medical practice in order to ascertain what percentage of diabetes patients would be suitable to join the programme. Potential participants will be excluded based on the criteria below.

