### Exclusion criteria

Persons will be ineligible for the study if:they are aged less than 18 yearsthe consulting medical practitioner considers that an alteration in nutrient or calorie consumption or that participating in regular moderate exercise could result in an increased health risk. This may include but may not be limited to:i.persons having a history of uncontrolled hypertension with consistent resting blood pressure readings greater than 180 mmHg systolic and or greater than 110 mmHg diastolic;ii.persons having a BMI lower than 21 kg/m^2^, and making use of weight-loss medication;iii.persons experiencing recurrent chest pain or unstable angina;iv.pregnant or lactating females, or females planning to become pregnant in the next year;v.persons who have undergone angioplasty or experienced a myocardial infarction or cardiac surgery within the previous three months;they have any condition that precludes them from increasing their level of physical activity;they have any physical condition or language barrier that would preclude them from understanding or safely adopting the lifestyle changes recommended by the CHIP intervention.

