### Sample size estimate

The total sample required for this study is 150, with an equal number of participants in each arm of the study. The sample size was calculated on the following assumptions: a reduction in 3.5% of fasting glucose in the intervention group, an equal allocation of participants to each group as well as a 10% drop out rate. A standard deviation of 20 was used. This study is sufficiently powered d > 80% to detect a 3.5% reduction in fasting glucose using significance of 0.05 (95% confidence interval).

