### Statistical analysis

All data collected will be coded and entered into IBM® SPSS® version 22 for Windows® (SPSS Inc., 2013) before analysis.

#### Analysis for research question 1 and 2

Descriptive statistics will be used to analyze demographic data, anthropometric measurement data, blood results and activity levels on commencement of the program and also at the described re-evaluation intervals. Descriptive statistics will include frequencies, percentage distribution, means, and medians as well as standard deviation from the mean.

The Shapiro-Wilk test will be used to determine normal distribution to decide on whether to use parametric or non-parametric testing for correlations and variance analysis. A paired sample t-test (dependent t-test) will be used to compare pre intervention data with post intervention (12 weeks) and pre intervention data with post intervention (12 months) data. An independent t-test will be used to compare data between intervention and control groups. Pearson’s correlation will be used to explore relationships between continuous variables. The dietary inventory, health survey, and quality of life survey will be independently scored and the results between groups compared using linear regression. The level of significance is set at *p* < 0.05.

#### Analysis for research question 3

To determine the cost benefit of the intervention, a cost-benefit analysis will be undertaken. The cost benefit analysis will involve assessment of beneficial effects of the intervention. The analysis will include benefits and costs attributed to the project and indirect costs. Therefore, where B represents all the benefits and C represents all the costs, the project will be considered beneficial if B-C > 0. A cost benefit ratio will also be calculated. Costs included in the analysis will include opportunity costs. Costs from published literature and from government agencies will be used wherever possible, for example, the Medical Benefits Scheme and Pharmaceutical Benefits Scheme.

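### Aim 1 speaks of reversing abnormal fasting glucose, but the entry criteria, research question, sample size target and analysis all concern a change in glucose level

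*Protocol article*

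**What the plan says.** - **Aim** (Aims and research questions): "To assess the effectiveness of the CHIP intervention in reversing abnormal fasting blood sugar levels in people with T2DM". The article defines neither the abnormal state nor its reversal.
- **Research question 1** (same section): compared with routine care, "what changes occur in fasting blood sugar levels (FBSL), HBA1c" and the other listed measures. It asks about change in level and sets no threshold.
- **Entry** (Study participants): "Patients, who have a diagnosis of T2DM will be recruited from general practice medical centers". The abstract likewise describes "150 individuals with an established diagnosis of T2DM".
- **Exclusions** (Exclusion criteria): the list opened by "Persons will be ineligible for the study if" covers age, medical risk, inability to increase activity, and physical or language barriers. No item concerns fasting glucose, HbA1c or glucose-lowering treatment.
- **Planning effect** (Sample size estimate): "a reduction in 3.5% of fasting glucose in the intervention group".
- **Analysis** (Statistical analysis): "An independent t-test will be used to compare data between intervention and control groups". Paired t-tests compare baseline with 12 weeks and with 12 months.
- **Related provisions**: Data collection records blood tests and medication use at baseline, 12 weeks and 12 months. Medical management of participants sends them to their general practitioner for any medication change that glucose or blood pressure readings call for.

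**The concern.** Reversal of an abnormal value has two parts: the value is abnormal at the start, and it is no longer abnormal later. The stated design secures neither. A person with diagnosed diabetes whose fasting glucose is in range at entry, for example on treatment, is eligible and has no abnormal value to reverse. The comparison of arms is a comparison of mean levels, which does not record whether anyone moved from abnormal to normal.

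What is at stake is the conclusion drawn under aim 1. The article says that its outcomes may inform treatment decisions and encourage funding of lifestyle programmes. Those readers would take a finding that the programme reverses abnormal glucose differently from a finding that it lowers average glucose.

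**Working it through.** **Step 1: set the parts side by side.**

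| Element | What aim 1 needs | What the article states |
|---|---|---|
| Population | Abnormal fasting glucose at baseline | Diagnosed type 2 diabetes, no glucose condition |
| Outcome | Abnormal value becomes normal | Change in fasting glucose level |
| Planning effect | Difference in proportion reversed | 3.5% reduction in fasting glucose |
| Comparison | Proportions between arms | Independent t-test between arms, paired t-tests within arm |

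The right-hand column is consistent with itself and with research question 1. Only the wording of aim 1 stands apart.

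**Step 2: what a significant t-test would establish.** The independent t-test addresses whether mean fasting glucose differs between arms. The same mean difference can arise when many participants fall a little and stay abnormal, when some fall far enough to become normal, or when part of the fall occurs in people already in range. The test does not separate these cases. The paired tests do not help, because they compare time points within an arm and also concern means.

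**Step 3: the plan's own figure.** The article gives 150 participants (75 per arm), power above 80%, significance 0.05, SD 20 without a unit, and 10% dropout. Reading the difference as 3.5 on the scale of that SD, two-sided:

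n per arm = 2 × [20 × (1.960 + 0.842) / 3.5]² ≈ 513, so 1,026 in total, and 1,026 / 0.9 = 1,140 after dropout.

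The 150 is not reproduced on this reading. The unit and baseline mean are not given, so other readings are possible. This is a separate matter. The present point does not depend on the sample size and would hold if 150 were correct.

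**Step 4: how informative a reversal comparison could be.** 75 × 0.9 = 67.5, so take 67 evaluable per arm, two-sided 0.05, 80% power, and the normal approximation for two proportions:

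power = Φ{ [(p2 − p1)√n − 1.960 √(2p̄(1 − p̄))] / √(p1(1 − p1) + p2(1 − p2)) }

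For p1 = 0.10 and p2 = 0.295, p̄ = 0.1975: (0.195 × 8.185 − 1.960 × 0.563) / 0.546 ≈ 0.90, which gives power of about 0.82. Searching in steps of half a percentage point for the first rate that reaches 80%:

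| Assumed control proportion | Intervention proportion needed |
|---|---|
| 5% | 21.5% |
| 10% | 29.5% |
| 20% | 42.5% |
| 30% | 54% |

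The control proportions are assumptions; the article gives none. The table uses all 67 per arm. Restricting to those abnormal at baseline leaves fewer, so larger differences would be needed.

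**The case against.** The strongest reply is that the operative question is already stated and the design fits it. Research question 1 asks about change in fasting glucose against control, and the population, planning effect and t-tests all serve that question. The verb in the aim may be loose wording for lowering. A responder definition is also something that a full protocol or analysis plan, not shown here, could supply. Broad entry is a legitimate choice for a trial in general practice.

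Most of this stands. The absence of a reversal endpoint is not itself the finding, and neither is the breadth of entry. What remains is a conflict between parts that the article does state. If the verb is loose, rewording it is the remedy.

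A reader might infer more in three ways, and the documents do not support any of them.

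- *That even a positive trial could never support reversal.* Individual glucose values are collected at three time points, so a reversal analysis is possible. The limit applies to the stated analysis.
- *That a 3.5% fall could normalise only patients just above a threshold.* The 3.5% is a planning figure. It does not cap the true effect and is not a fall applied to each patient. Individual changes will vary.
- *That patients already controlled dilute the effect by a calculable amount.* The article gives neither their share nor their expected change, and the 3.5% may already be an average over all diagnosed patients.

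**Conclusion.** The point holds as a mismatch between aim 1 and the rest of the plan. The stated analysis, if significant, supports a conclusion that fasting glucose was lower with the programme than with usual care. It does not by itself support a conclusion that abnormal glucose was reversed. This rests on reading reversal in its ordinary sense of abnormal becoming normal; if the sponsor means only lowering, the defect is one of wording. It cannot be said that the trial would be reported as showing reversal, since the article's planned conclusions make no such claim. The matter should be settled before data exist, and according to Study status recruitment was only about to begin.

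**What to change.** **Preferred.** Reword aim 1 and the matching conclusion to lowering fasting blood sugar relative to usual care. Make the between-arm comparison of fasting glucose in all randomised participants the main analysis for it. The Interventions section removes from the study participants who receive less than 80% of the programme, so that rule must be reconciled with an all-randomised analysis. Rewording the aim costs nothing in visits or patients.

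**If the reversal aim is kept.** Add a prespecified secondary comparison:

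- State one fasting glucose threshold and the follow-up time point.
- Among randomised participants at or above the threshold at baseline, compare between arms the proportion below it at follow-up.
- Report change in glucose-lowering medication alongside. Medication use is already collected, and the plan allows it to change, so a value brought into range by added drugs should not be read as an effect of lifestyle.

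This uses data already collected. The cost is precision: the comparison uses a subset and a dichotomised outcome, so its power is low. Report it as an estimate with its confidence interval, and do not treat a non-significant result as evidence against reversal.

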### Study design

A parallel randomized control study design will be used. A cohort of 150 patients will be randomized into either an intervention or control group. There will be 75 participants in each of the two groups. For the purpose of this study Group 1 will be the intervention group and Group 2 the control group.

### Study setting

The CHIP intervention will be conducted by CHIP trained volunteers in selected community halls on the Central Coast of NSW. A demographic and lifestyle survey will be administered at the venue the intervention is conducted. Anthropometric measurements and blood collection will occur at the venue at which the CHIP intervention is being conducted unless the facility is not suited for medical data collection in which case it will be collected at selected general practices.

### Study participants

Patients, who have a diagnosis of T2DM will be recruited from general practice medical centers (where practitioners have agreed to refer) on the Central Coast of NSW, Australia. Recruited patients will be invited to participate in the study. Enrollment of consenting participants will continue until the required sample size is met. The source population will be monitored at each participating General medical practice in order to ascertain what percentage of diabetes patients would be suitable to join the programme. Potential participants will be excluded based on the criteria below.

### Exclusion criteria

Persons will be ineligible for the study if:they are aged less than 18 yearsthe consulting medical practitioner considers that an alteration in nutrient or calorie consumption or that participating in regular moderate exercise could result in an increased health risk. This may include but may not be limited to:i.persons having a history of uncontrolled hypertension with consistent resting blood pressure readings greater than 180 mmHg systolic and or greater than 110 mmHg diastolic;ii.persons having a BMI lower than 21 kg/m^2^, and making use of weight-loss medication;iii.persons experiencing recurrent chest pain or unstable angina;iv.pregnant or lactating females, or females planning to become pregnant in the next year;v.persons who have undergone angioplasty or experienced a myocardial infarction or cardiac surgery within the previous three months;they have any condition that precludes them from increasing their level of physical activity;they have any physical condition or language barrier that would preclude them from understanding or safely adopting the lifestyle changes recommended by the CHIP intervention.

### Allocation of participants to a study group

Invitees who are willing to participate will be recorded on a list until such time as there are between 30 and 40 individuals listed. At this point, the individual participants will be randomized into either Group 1 or Group 2.

Once allocated, participants in Group 1, will receive the CHIP intervention over a period of 12 weeks. At the end of the 12 weeks period, Group 1 will receive monthly follow-up for a further 9 month period. This process will be repeated, until the full number of participants have been collected and assigned.

An overview of the study design and allocation of participants is illustrated in Fig. 1.

**Fig. 1 Fig1:**
[figure not shown]
An overview of the study design and allocation of participants

### Randomisation

The randomisation of participants will be performed by a person independent of the research team. The process of randomisation will occur with the aid of a computer. No blinding will be applied.

### Interventions

#### Group 1- intervention group

All participants in Group 1 will participate in the CHIP intervention for 12 weeks. The CHIP intervention consists of 18 education sessions, each of 90 min duration. Approximately half of each session is devoted to viewing pre-recorded visual material delivered by lifestyle medicine professionals, while interactive group discussions and activities, including food preparation and exercise demonstrations delivered by CHIP trained volunteers, make up the remaining time. An outline of the topics covered over the 18 sessions can be viewed in Table 1.

**Table 1 Tab1:** CHIP sessions as per topic

Session number	Topic
1	The rise of chronic disease
2	Lifestyle as medicine
3	The common denominator of chronic disease
4	The optimal lifestyle
5	Eat more, weigh less
6	Fibre, your new best friend
7	Disarming Diabetes
8	The heart of the matter – heart healthy
9	Controlling blood pressure and discovering protein
10	Bone health essentials
11	Cancer prevention
12	Understanding your results and taking action
13	Become what you believe. Your DNA is not your destiny
14	Practicing forgiveness
15	Re-engineering your environment
16	Stress relieving strategies
17	Fix how you feel
18	From surviving to thriving

Sessions 1 to 11 provides information on the aetiology, risk factors and pathological mechanism responsible for lifestyle related chronic disease. Emphasis is placed on the links between obesity, diabetes, hypertension, hyperlipidaemia and cardiovascular disease. Participants are provided with information relating to how lifestyle changes, particularly in diet and levels of physical activity, can positively alter the risk factors for as well as the course of chronic diseases. Specifically, the adoption of a plant-based, restricted sugar and salt diet is encouraged as well as daily physical activity involving a combination of aerobic and strengthening exercise most days of the week. Sessions 12 to 18 provide information related to other important lifestyle behaviors like substance use, rest, and sleep and stress management. Participants are provided with strategies that will assist them in assuming a position of control of their health, to overcome barriers, to manage and maintain behavior change and to cope with environmental pressures and stressors. At the end of the 12-week program, participants will be contacted for the purpose of assessing compliance and providing motivation and support on a monthly basis for an additional 9 months. Participants who receive less than 80% (4 sessions) of the program content will be regarded as having dropped out from the intervention and therefore will be excluded from the study. Self reported reasons for dropout will be noted.

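### The attendance cut-off for dropout pairs 80% with 4 sessions of an 18-session programme; the two figures agree only if the 4 are sessions missed, which the text does not say

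*Protocol article*

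**What the plan says.** All the relevant text is in the protocol article.

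- The Group 1 subsection under Interventions fixes the length of the programme: "The CHIP intervention consists of 18 education sessions, each of 90 min duration". Table 1 lists sessions 1 to 18.
- The same subsection gives the threshold as "Participants who receive less than 80% (4 sessions) of the program content". Those below it "will be regarded as having dropped out from the intervention and therefore will be excluded from the study".
- Study design gives the arm size: "There will be 75 participants in each of the two groups".
- The Group 2 subsection gives controls usual care and no programme sessions, so an attendance rule can apply only to Group 1.
- Randomisation says there is no blinding.

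The threshold is not restated anywhere else in the article.

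**The concern.** The percentage and the session count are offered as equivalents, and the verb concerns content received. Taken that way they are not equivalent, because four sessions is less than a quarter of the programme.

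The sentence is an operative rule. It decides which randomised participants in the intervention arm are removed, and nothing comparable can remove anyone from the control arm. Staff and analysts know the allocation, so a cut-off that can be read more than one way could be interpreted with results in view. Any removal of poor attenders also makes the two arms less comparable than randomisation left them. An exclusion rule of this kind should therefore have a single meaning before recruitment starts.

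**Working it through.** **Inputs.** Number of sessions S = 18, all of equal length (90 min), from the Group 1 subsection and Table 1. Threshold: below 80%, glossed as 4 sessions, same subsection. Arm size 75, from Study design.

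**Step 1: try to reproduce the stated equivalence.** As sessions received, 4/18 = 0.222, or 22.2%. This is not 80%, so the stated pair is not reproduced.

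**Step 2: convert 80% to sessions.** 0.80 × 18 = 14.4. Measuring content by time gives the same answer: 18 × 90 = 1,620 min, 0.80 × 1,620 = 1,296 min, and 1,296/90 = 14.4. In whole sessions, 14/18 = 77.8% is below the threshold and 15/18 = 83.3% is above it. Below 80% therefore means 14 or fewer attended.

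**Step 3: convert the shortfall.** 0.20 × 18 = 3.6, so the first whole number of missed sessions that puts someone below 80% is 4. This is the probable origin of the 4.

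**Step 4: compare each reading of the 4 with the percentage rule, for every attendance count from 0 to 18.**

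| Reading of the 4 | Dropout if attended | Counts classified differently from below 80% |
|---|---|---|
| Fewer than 4 received (as written) | 0 to 3 | 4 to 14 |
| 4 or more missed | 0 to 14 | none |
| More than 4 missed (4 absences allowed) | 0 to 13 | 14 only |

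**Step 5: size of the doubt that remains on the missed reading.** It concerns only people who attend exactly 14. The article gives no attendance figures, so this step rests on an assumption: each session is attended independently with the same probability p. Then P(exactly 14 of 18) = C(18,14) × p^14 × (1 − p)^4, with C(18,14) = 3,060.

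| Assumed p | P(exactly 14) | Expected number of 75 |
|---|---|---|
| 0.80 | 0.215 | about 16 |
| 0.85 | 0.159 | about 12 |
| 0.90 | 0.070 | about 5 |

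Real attendance tends to cluster within people, so these values are illustrative.

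**The case against.** The strongest reply is that this is a missing word. If the 4 are sessions missed, then 4 or more missed and below 80% classify every possible attendance count identically. Moreover, 80% and 18 are both stated, so the percentage gives one answer without the parenthesis. Most of this stands. The missed reading is the likely intent, and on it the two figures do not conflict.

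It does not remove the point. The sentence speaks of content received and never mentions absence. A reader who does supply the missing word must still decide whether the fourth absence is the first that disqualifies or the last that is allowed.

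Three stronger readings are tempting, and the document does not support them:

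- A reader might infer that the two figures define very different groups. On the same binomial assumption, with p from 0.90 to 0.80, the 80% rule would class about 7 to 37 of 75 as dropouts (P(14 or fewer) = 0.098 to 0.499), and a rule of fewer than 4 received almost none. That contrast needs the received reading, under which the authors would be equating 4 of 18 with 80%. It also needs attendance rates the article does not give. It is not a measure of the likely error.
- A reader might infer that the cut-off determines the compliance result for research question 2. The research questions ask for compliance levels over 12 months, and the Group 1 subsection describes compliance being assessed at the monthly contacts after the programme. Neither is tied to this threshold.
- A reader might object that the article does not say whether a session made up later counts as received. That is operational detail an article commonly leaves to the full protocol, and it is not a fault here.

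**Conclusion.** The point holds in limited form. As written, the count in parentheses is wrong for the percentage it glosses: 22.2% against 80%, or 4 sessions against 14.4. This follows from the article's own figures and needs no assumption. The figures reconcile if the 4 means 4 or more missed, so the fault is most likely one of drafting. What then remains open is the classification of those who attend exactly 14 sessions. The 5 to 16 of 75 attached to that group depends on the assumed attendance probabilities and on independence between sessions.

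It deserves correction because the sentence is a decision rule that removes randomised participants from one arm of an unblinded trial, and no other text in the article corrects it.

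**What to change.** Replace the percentage and the parenthesis with a single count of sessions attended out of 18, and name the boundary case explicitly. If the stated 80% is what is meant, dropout from the programme is 14 or fewer of 18 attended, that is, 4 or more missed, so a participant who misses exactly 4 falls below the threshold. If four absences were meant to be allowed, the percentage must change instead, because 14/18 is 77.8%.

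In the same sentence, limit the use of the threshold to defining a per-protocol set and describing attendance, and keep every randomised participant in the main comparison between groups whatever their attendance. Outcome measurements at 12 weeks and 12 months should then still be sought from low attenders.

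The cost is one sentence, settled before recruitment begins, plus the follow-up of low attenders at time points already scheduled for both groups. No change to the sample size or the intervention is needed for this point.
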